## Abstract

**Background:**

There is a consensus that exercise therapy should be used as a therapeutic approach in chronic low back pain (CLBP) but little consensus has been reached about the preferential type of therapy. Due to the heterogeneity of the population no clear effect of specific therapy interventions are found. Probably a specific subgroup of the investigated population will benefit from the intervention and another subgroup will not benefit, looking at the total investigated population no significant effects can be found. Therefore there is a need for the development of clinical prediction rules (CPRs). Objectives for this trial are first, the derivation of CPRs to predict treatment response to three forms of exercise therapy for patients with nonspecific CLBP. Secondly, we aim to validate a CPR for the three forms of exercise therapy for patients with nonspecific CLBP.

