**Methods/Design:**

The study design is a randomized controlled trial. Patients with nonspecific CLBP of more than three months duration are recruited at the Antwerp University Hospital (Belgium) and Apra Rehabilitation Hospital. After examination, patients are randomly assigned to one of three intervention groups: motor control therapy, general active exercise therapy and isometric training therapy. All patients will undergo 18 treatment sessions during nine weeks. Measurements will be taken at baseline, nine weeks, six months and at one year. The primary outcome used is the Modified Oswestry Disability Questionnaire score. For each type of exercise therapy a CPR will be derived and validated. For validation, the CPR will be applied to divide each treatment group into two subgroups (matched and unmatched therapy) using the baseline measurements. We predict a better therapeutic effect for matched therapy.

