### Data analysis

#### Derivation phase

This phase aims to detect potential predictive variables for treatment success (dichotomous, yes or no) in a set of baseline measurements. A minimal decrease in the MODI score of six points is considered as treatment success [35].

Potential predictive variables are selected as follows: first, individual variables from the self-reports, history and physical examination are tested for their bivariate association with the reference standard using independent sample t tests, Mann-Whitney U tests or chi-square tests based on the nature of the data. Variables with a significance level of *P* <0.10 are retained as potential prediction variables. We chose a more liberal significance level at this stage to avoid excluding potential predictive variables.

Next, selected potential prediction variables and known predictors as determined in the study of Hicks *et al*. [16] are entered into a multiple linear regression equation to determine the optimal set of predictors. A significance of *P <*0.05 is used in this stage. Variables retained in the regression model are used to develop a multiple CPR for classifying patients as likely responders to treatment. This statistical analysis is performed for each treatment group (motor control therapy, general active exercise therapy and isometric training therapy).

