#### Validation phase

In the validation phase new patients will be again assigned randomly into one of the three treatment groups. Based on the derived CPR determined in phase one, each intervention group will be divided into either ‘matched therapy’ or ‘unmatched therapy’. The recruitment, information form, informed consent, measurements, blinding and intervention procedure will be the same for both derivation and validation phase.

To verify intergroup differences at baseline, variables will be compared between groups using independent t tests, Mann-Whitney U tests, or chi-square tests of independence based on the nature of the data.

To examine the principle hypothesis (difference in treatment effect between matched and unmatched groups), a three-way repeated-measures analysis of variance will be performed with treatment group (motor control versus general active exercise therapy vs. isometric therapy) and classification subgroup (motor control versus general active exercise therapy versus isometric therapy) as between-subject variables and time (baseline, nine weeks, six months and one year) as the within-subject variable. The dependent variable is disability (MODI score). The hypothesis of interest is the three-way interaction, and the two-way interactions between time and treatment group and between time and classification subgroup. We hypothesize that outcome over time will not differ based on the randomized treatment group, or the classification subgroup, but will depend on the interaction between the treatment group and classification subgroup, such that patients randomized to matched treatment will have better outcomes than patients randomized to unmatched treatment. This hypothesis will be supported if the three-way interaction is significant, but the two-way interactions are not. Pairwise *post-hoc* comparisons will be performed at each follow-up period to further explore any significant interaction terms. In both the derivation and validation phase we will use an intention-to-treat analysis.

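### The plan promises to validate a rule for each of three therapies, but its only success criterion is global and cannot say which rule works

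*Protocol article*

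**What the plan says.** Abstract, Methods/Design: "For each type of exercise therapy a CPR will be derived and validated". The derivation part of Data analysis carries this out by repeating the variable selection and regression within each treatment group, which gives three rules.

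The validation part of Data analysis poses one question: "To examine the principle hypothesis (difference in treatment effect between matched and unmatched groups), a three-way repeated-measures analysis of variance will be performed". The between-subject factors are randomised therapy (three levels) and classification (three levels), with "time (baseline, nine weeks, six months and one year) as the within-subject variable". The decision rule is: "This hypothesis will be supported if the three-way interaction is significant, but the two-way interactions are not". After that, "Pairwise *post-hoc* comparisons will be performed at each follow-up period to further explore any significant interaction terms".

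The section names no contrast for an individual rule, no visit that decides, and no multiplicity adjustment for the pairwise comparisons. It does not say that they are unadjusted.

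**The concern.** The objective is stated per therapy and the decision rule is stated once for all therapies. The interaction is an F test with (3−1)×(3−1)×(4−1) = 12 numerator degrees of freedom. A significant result says that some departure from additivity exists at some visit. It does not say which rule produced it, or whether matched patients did better or worse.

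The product of the trial is guidance on choosing among three therapies. Followed as written, the plan can report the matching hypothesis as supported when the rule for one or two of the therapies has no value. The only way to find out which is a set of exploratory comparisons at three follow-ups, which may disagree with each other.

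**Working it through.** **Inputs from the article.** 105 completers, 35 per therapy, effect size 0.43, 54% dropout (Power analysis, Validation phase); a 50:50 matched:unmatched split within each therapy (Randomization and blinding); four visits and the criterion above (Data analysis).

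**Assumed.** Alpha 0.05 for the validation tests (not stated for this phase); correlation 0.5 between visits with compound symmetry; each patient classified to exactly one therapy; a working rule k shifts MODI by d SD only where class k receives therapy k, equally at all three follow-ups.

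**The plan's own figure.** The dropout step reproduces: 105/(1−0.54) = 228.3, so 229. The 105 does not reproduce as a one-tailed two-group comparison: 2×(1.645+0.842)²/0.43² = 66.9, so 67 per group, 134 in all. That is a separate matter; the 105 is taken as given here.

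**Step 1: how often the full criterion is met when some rules do not work.** Both parts of the criterion were simulated: three-way interaction significant, both two-way interactions with time not.

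| Rules that work | d (SD) | Three-way significant | Full criterion, equal cells of 12 |
|---|---|---|---|
| One | 0.43 | 9% | 8% |
| One | 0.8 | 25% | 17% |
| One | 1.0 | 40% | 21% |
| One | 1.3 | 66% | 20% |
| One | 1.8 | 94% | 6% |
| Two | 0.8 | 61% | 41% |
| Two | 1.0 | 85% | 45% |
| Two | 1.3 | 99% | 32% |

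Within simulation error these are the summary ranges of 6–22% (one rule) and 33–45% (two rules). With the 50:50 split the cells are unequal, and the result depends on how the two-way terms are tested. Adjusted for every other term, the ranges are 7–24% and 35–51%. Tested in a model without the three-way term, they are 1–14% and 17–39%.

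At large d the criterion fails for the opposite reason. An effect confined to one cell also feeds the two-way terms, so a strongly working single rule is usually not declared supported.

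**Step 2: what the pairwise comparisons add.** If no rule works, requiring a significant interaction first keeps error low: interaction plus any of the nine matched-v-unmatched tests (3 rules × 3 follow-ups) is significant in 1.4–2.8% of trials (correlation 0.7 to 0.3). Once one rule works, that gate no longer protects the other two. Given a significant interaction, a useless rule shows a nominally significant benefit at some follow-up, without adjustment, in roughly 13–20% of trials. Jointly with the full criterion this happens in only about 0.5–3%.

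**Step 3: power of a test per rule.** With a 50:50 split of 35, each therapy has about 17.5 matched and 17.5 unmatched patients. If the unmatched divide evenly between the other two classes, class k has 17.5 patients on therapy k and 2×8.75 = 17.5 on the others. Power is Φ(d√(n/2) − z), with 0.43×√8.75 = 1.272:

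- One-sided 0.05: Φ(1.272−1.645) = 35% (exact t: 34%).
- Two-sided 0.05: Φ(1.272−1.960) = 25% (exact t: 23%).
- First Holm step, 0.05/3, one-sided: Φ(1.272−2.128) = 20% (exact t: 18%).
- First Holm step, two-sided: Φ(1.272−2.394) = 13% (exact t: 12%).

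For 80% power per rule at one-sided 0.05/3: 2×(2.128+0.842)²/0.43² = 95.4, so 96 per arm and 96×2×3 = 576 completers, against 105 planned.

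**The case against.** The strongest reply is that the principal hypothesis is pooled. The data analysis section defines it as matched against unmatched, the sample size rests on that comparison, and the abstract's objective is looser: "Secondly, we aim to validate a CPR for the three forms of exercise therapy for patients with nonspecific CLBP". On that reading no per-rule test was promised. This carries weight, and it is why narrowing the claim is an acceptable remedy. But the abstract's Methods/Design sentence is explicit that each therapy gets a validated rule, and the derivation is done separately by therapy. The two statements need reconciling either way.

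A second reply is that requiring non-significant two-way interactions blocks the single-rule scenario. It does reduce it, sharply for large effects, as the table shows, but it does not remove it and does little when two of three rules work.

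A reader might go further and infer that a battery of uncorrected pairwise tests will be used to declare rules validated, with a grossly inflated error rate. The article does not support that. It is silent on adjustment, which a condensed article may leave to the full analysis plan. It describes the comparisons as exploring a significant interaction, not as validation tests. They are run only after such an interaction, which holds error down when no rule works. Error rates computed without that gate do not describe this plan.

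**Conclusion.** The concern holds as a mismatch between objective and criterion. Three rules are to be validated, and the one stated criterion is global and non-directional, so support driven by one or two rules would be read as support for all three. Under the assumptions above this occurs in about 6–22% of trials with one working rule and 33–45% with two; cell layout and the form of the two-way tests widen these to about 1–24% and 17–51%. The figures depend on the assumed alpha, correlation and effect pattern. The absence of a per-rule criterion does not: it is fixed in the text, and an analysis plan faithful to the article would inherit it.

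The multiplicity element is secondary. A useless rule may look beneficial in roughly 13–20% of trials with a significant interaction, but in only about 0.5–3% jointly with the full criterion. This should be corrected before the validation phase is analysed.

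**What to change.** In Data analysis, Validation phase:

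1. State that the three-way interaction, or a pooled matched-v-unmatched result, supports matching in general and does not validate each rule.
2. For each rule, name one directional contrast at one pre-named visit: among patients classified to therapy k, MODI on therapy k against MODI on the other two therapies, adjusted for baseline MODI. This compares randomised patients; the analysis should respect the allocation ratio that the 50:50 stratification creates.
3. Test the three contrasts with Holm at an overall 5%, and call a rule validated only on its own contrast in favour of matching.
4. Keep other visits and cell pairs exploratory, reported as estimates with confidence intervals.

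This costs wording and a few model contrasts, with no new patients or measurements. The downside is the low power per rule in step 3 of the working, so a null contrast would not show that a rule fails. The article should therefore say that per-rule validation is limited at this sample size, or narrow the abstract's sentence to the overall matching effect.

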#### Validation phase

In the validation phase the intervention therapy stays the same, but new patients will be included. In this study design, the interest is that treatment success will be higher in the matched group than the unmatched group, which means a one-tailed hypothesis is used to calculate the power. In the validation phase we need 105 patients to detect a minimum clinically important difference (effect size 0.43) with 80% power using a one-tailed hypothesis. This means that three groups of 35 patients are needed to complete the whole trial. Again we assume a dropout rate of 54% into account and therefore aim to include 229 patients.

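### The validation phase claims intention-to-treat but tests its principal hypothesis with a repeated-measures ANOVA that, run as named, uses only patients with MODI at all four time points

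*Protocol article*

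**What the plan says.** All references are to the protocol article.

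- **Method.** Under Data analysis, Validation phase, the principal hypothesis (matched versus unmatched therapy) is to be examined as follows: "a three-way repeated-measures analysis of variance will be performed". Treatment group and classification subgroup, each with three levels, are the between-subject factors. The within-subject factor has four levels: "time (baseline, nine weeks, six months and one year) as the within-subject variable". The dependent variable is the MODI score.
- **Population.** The same section closes with: "In both the derivation and validation phase we will use an intention-to-treat analysis".
- **Sample size.** Under Power analysis, Validation phase: "In the validation phase we need 105 patients to detect a minimum clinically important difference". The article then adds: "This means that three groups of 35 patients are needed to complete the whole trial". The recruitment target follows from an allowance for loss: "Again we assume a dropout rate of 54% into account and therefore aim to include 229 patients".
- **Follow-up.** Under Measurements, Follow-up, MODI is collected at nine weeks, six months and one year. Patients are contacted by mail for the two later visits, and by phone if they do not reply.

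The article names no mixed model, imputation or other device that would bring a patient with a missing visit into the ANOVA.

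**The concern.** Three stated elements do not fit together: a method that needs complete data, an intention-to-treat population, and an expected loss of more than half the patients.

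Two things are at stake:

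- **Protection by randomisation.** Whether a patient receives matched or unmatched therapy is decided by random allocation. Completers are selected after that allocation. If patients who do badly tend to leave, and matching affects how they do, matched and unmatched completers are no longer comparable groups. Recruiting more patients restores the number analysed but does not remove this selection.
- **Data already collected.** A patient with a nine-week MODI who misses only the one-year contact is removed from the whole analysis, including its nine-week part.

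**Working it through.** **Inputs from the article:** 105 patients needed in the validation phase (3 x 35); dropout 54%; target 229; four time points; 3 treatment groups x 3 classification subgroups; effect size 0.43; one-tailed test.

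**1. Reproduce the plan's target.** 105 / (1 - 0.54) = 105 / 0.46 = 228.3, rounded up to 229. This matches the article.

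**2. Number with complete data.** Assume that dropout means a missing MODI at one or more visits. Then 229 x 0.46 = 105.3, so about 105 are complete, and 229 - 105 = 124 (54%) are left out of an ANOVA run on complete cases. Over the nine treatment-by-classification cells the average is 105 / 9 = 11.7 complete cases, against 229 / 9 = 25.4 randomised.

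**3. What the discarded visits could hold.** The timing of dropout is not given, so these patterns are assumptions. Each ends at 54% by one year.

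| Assumed cumulative dropout at 9 weeks / 6 months / 1 year | Patients with MODI at each visit | Complete cases |
|---|---|---|
| 54% / 54% / 54% | 105 / 105 / 105 | 105 |
| 18% / 36% / 54% | 188 / 147 / 105 | 105 |
| 0% / 0% / 54% | 229 / 229 / 105 | 105 |

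The complete-case count is the same in every pattern. The follow-up data thrown away range from none (all loss before nine weeks) to the nine-week and six-month scores of all 124 patients.

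**4. Illustration of the information at nine weeks.** This is a two-group t test of matched versus unmatched with equal groups, in line with the planned 50:50 pre-stratification. The standardised difference is 0.43. One-sided alpha 0.05 is assumed, because the article states one-tailed but gives no alpha. Power is the probability that a noncentral t with N - 2 degrees of freedom and noncentrality 0.43 x sqrt(N / 4) exceeds the critical value.

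| Patients with nine-week MODI | Noncentrality | Power |
|---|---|---|
| 105 (completers) | 0.43 x sqrt(105 / 4) = 2.20 | 71% |
| 70% of 229 = 160 (assumed) | 0.43 x sqrt(160.3 / 4) = 2.72 | 86% |
| 85% of 229 = 195 (assumed) | 0.43 x sqrt(194.65 / 4) = 3.00 | 91% |

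This is not the planned three-way interaction test. It only shows how much information the discarded nine-week scores could carry.

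**The case against.** - **The article nowhere says that incomplete patients are excluded.** This is correct. Exclusion is a property of the named method, not a sentence in the text. A reader might infer that the plan will definitely analyse only 105 patients, and the documents do not support that. A full protocol or analysis plan that is not shown could specify imputation, and an ANOVA on imputed data would be compatible with intention-to-treat. The absence of a missing-data section is therefore not the point. The point is that the method and the population, both stated, conflict at the stated dropout unless something further is specified.
- **Inflating for dropout does not prove a completer analysis.** This is also correct. Such inflation is routine under any analysis, including a mixed model. The step from 105 to 229 shows how many completers the plan expects, not that only they will be analysed.
- **The 54% may not mean missing MODI.** It comes from a cited study, and elsewhere (Intervention, Motor control therapy) the article speaks of drop-out in connection with compliance with treatment. Patients who stop treatment but still attend visits would raise the number analysed. Reading 54% as lost outcome data is plausible, because the article speaks of patients needed to complete the trial, but it is an assumption.
- **The bias may be small.** It could be. Its size depends on when and why patients leave, which the article does not say, so no figure for it is given here.
- **The intention-to-treat sentence covers both phases.** A reader might extend the criticism to the derivation phase. The text does not support that: the derivation analysis does not use this ANOVA and does not say that only completers are used.

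**Conclusion.** The concern holds for the validation phase. As named, the principal analysis needs MODI at all four time points, and this cannot be reconciled with the stated intention-to-treat population when 54% dropout is expected. If dropout means at least one missing MODI, about 105 of 229 randomised patients would be analysed and about 124 left out, whatever the timing of the loss.

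That consequence rests on two assumptions: that the ANOVA is run in its standard form without imputation, and that dropout means missing outcome data. The 71% versus 86% to 91% power comparison also rests on an assumed alpha, assumed nine-week retention and a simpler test than the planned one, so it is an illustration only. If all loss came before nine weeks, little data would be recovered, but the conflict between method and population would remain. It is worth settling before analysis, because it concerns the principal hypothesis and possibly more than half the randomised patients.

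**What to change.** In Data analysis, Validation phase:

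1. Replace the repeated-measures ANOVA with a likelihood-based linear mixed model for repeated measures of MODI. Keep the treatment group x classification subgroup x time terms, so that the hypotheses of interest are unchanged.
2. State that every randomised patient is included in the assigned group with all available MODI values. Multiple imputation before the stated ANOVA would also resolve the conflict, if the ANOVA is to be kept.
3. Add a sensitivity analysis for dropout that is missing not at random.

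The cost is a change of wording, standard software and a little more analysis work. No new data are needed. The downside is that both the mixed model and standard multiple imputation rely on a missing-at-random assumption, which is the reason for the sensitivity analysis.

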### Information form and informed consent

If patients meet the inclusion and exclusion criteria they are scheduled for an interview with one of our researchers to be informed about the trial. If patients decide to participate they will sign an informed consent. Information form and informed consent are made and have been approved by the ethics committee of the University of Antwerp, the Antwerp University Hospital and Apra Rehabilitation Hospital.

## Discussion

The goal of this trial is the derivation and validation of a CPR for the choice of an exercise therapy type in nonspecific CLBP patients. Our study protocol differs from previous studies on several points.

First, a randomized clinical trial with several treatment options is used. So far, only one CPR for motor control therapy is derived in patients with non-radicular LBP [16]. A single-arm intervention study design was used. The derivation of a CPR for exercise therapy should be repeated in a randomized controlled trial design to confirm and reinforce findings. If a randomized controlled trial design is used, differences between different intervention groups can be made, and patients are randomly allocated into these groups to ensure there is no difference between the groups for success outcome.

Second, we target CLBP patients with a sufficiently long history of LBP. Hicks *et al*.’s [16] study sample had a mean duration of current symptoms for 40.6 days. Patients with symptoms for 40.6 days are classified as having sub-acute LBP [2]. Brennan *et al*.’s [17] study sample had a mean duration of current symptoms for 16 days, which are acute and sub-acute LBP problems [2]. In contrast, we aim to include patients with persisting LBP for at least three months to ensure we only target genuine CLBP patients [2]. We target CLBP patients because these patients are a big challenge for adequate treatment and they bring high health-related costs to society. Since both studies describe an acute and sub-acute study sample, our study results might differ from theirs [16, 17]. In conclusion we state that derivation, validation and impact phase of the development of a CPR for exercise therapy in a chronic LBP study sample has not yet been described in the literature.

Third, we aim to include a sufficiently large sample, based on a power analysis. Hicks *et al*. [16] included 54 patients in their study but no power analysis is mentioned in their paper. If there are not enough patients included, the CPR is unlikely to be valid. We compared our calculated sample size with the sample size calculated in Brennan *et al*.’s [17] study design and found comparable results. In addition, we use an extra 54% inclusion target to compensate for the possible dropout rate [34]. We aim to recruit 489 patients in total (combined total for both phases of the study). We calculated that each year around 200 LBP patients start the back revalidation program in the Antwerp University Hospital. This is the same for the Apra Rehabilitation Hospital. Out of these 400 LBP patients around 50% have nonspecific complaints. This means that we need around 18 months to finish each phase. We will closely follow the inclusion procedure to make sure we meet our goals. The current study protocol describes only the derivation and validation phase, and not the impact phase. Future research should target this impact phase. The impact phase needs a completely different approach since it investigates the economic consequences of the implication of the CPR. It also depends on the outcome of the derivation and validation phase. Consequently, it is beyond the scope of the present paper.

